# Evaluation of PET and laparoscopy in STagIng advanced gastric cancer: a multicenter prospective study (PLASTIC-study)

**DOI:** 10.1186/s12885-018-4367-9

**Published:** 2018-04-20

**Keywords:** Gastric cancer, Gastrectomy, Laparoscopy

## Abstract

**Background:**

Initial staging of gastric cancer consists of computed tomography (CT) and gastroscopy. In locally advanced (cT3–4) gastric cancer, fluorodeoxyglucose positron emission tomography with CT (FDG-PET/CT or PET) and staging laparoscopy (SL) may have a role in staging, but evidence is scarce. The aim of this study is to evaluate the impact and cost-effectiveness of PET and SL in addition to initial staging in patients with locally advanced gastric cancer.

**Methods:**

This prospective observational cohort study will include all patients with a surgically resectable, advanced gastric adenocarcinoma (cT3–4b, N0–3, M0), that are scheduled for treatment with curative intent after initial staging with gastroscopy and CT. The modalities to be investigated in this study is the addition of PET and SL. The primary outcome of this study is the proportion of patients in whom the PET or SL lead to a change in treatment strategy. Secondary outcome parameters are: diagnostic performance, morbidity and mortality, quality of life, and cost-effectiveness of these additional diagnostic modalities. The study recently started in August 2017 with a duration of 36 months. At least 239 patients need to be included in this study to demonstrate that the diagnostic modalities are break-even. Based on the annual number of gastrectomies in the participating centers, it is estimated that approximately 543 patients are included in this study.

**Discussion:**

In this study, it is hypothesized that performing PET and SL for locally advanced gastric adenocarcinomas results in a change of treatment strategy in 27% of patients and an annual cost-reduction in the Netherlands of €916.438 in this patient group by reducing futile treatment. The results of this study may be applicable to all countries with comparable treatment algorithms and health care systems.

**Trial registration:**

NCT03208621. This trial was registered prospectively on June 30, 2017.

## Background

Gastric cancer is the fifth most common type of cancer worldwide [1]. In Western countries, curative treatment consists of gastrectomy with perioperative chemotherapy [2–4]. Unfortunately, the prognosis of patients who undergo curative treatment remains relatively poor, with a 5-year overall survival rate of 20–40%. The main cause for this poor prognosis is tumor recurrence [2, 5]*.* The poor prognosis, treatment-related morbidity and mortality, and impairments in quality of life result in a high disease burden [6].

The standard diagnostic work-up of patients with gastric cancer includes a gastroscopy to assess tumor size and location and to obtain tissue to characterize the tumor. Furthermore, computed tomography (CT) of the thorax and abdomen is performed to detect metastases and evaluate local resectability. However, the accuracy of CT for detecting metastatic disease (M1) or local irresectability (T4b) is low: the sensitivity to detect peritoneal metastases is 22%–33%, to detect distant metastases is 14%–65% and to detect T4b disease is 5%–69% [7–10]. Consequently, two undesirable situations may occur in practice:

1. Unexpected intraoperative peritoneal metastases or local tumor irresectability are found at the onset of gastrectomy.

2. Undetected distant metastases presenting shortly after treatment with curative intent (neoadjuvant chemotherapy and/or surgery).

In both situations, patients undergo a futile treatment, probably leading to a reduced quality of life and an increase in health care costs.

A recent study from the United States investigated the additional staging capacities of fluorodeoxyglucose positron emission tomography with CT (PET) and staging laparoscopy (SL) in gastric cancer. In this study, combination of PET and SL identified additional metastases in 27% of patients: distant metastases by PET in 10% of patients, and peritoneal metastases by SL in 19% of patients (with an overlap of 2%) [11]*.*To reduce the number of patients undergoing futile treatment, the new Dutch guidelines for the treatment of gastric cancer recently included PET and SL in the staging algorithm of locally advanced (cT3–4) tumors“(http://www.oncoline.nl/maagcarcinoom)”. However, this guideline concludes that the evidence for both staging modalities is weak, and additional studies are needed to further investigate the cost-effectiveness and applicability of routinely adding PET and SL to the staging of locally advanced gastric cancer.

### Aim of the study

The aim of this study is to evaluate the clinical impact and cost-effectiveness of PET and SL in addition to initial staging by CT and gastroscopy in patients with locally advanced (cT3–4) gastric cancer.

## Methods

### Objectives

The primary outcome of this study is the proportion of patients in whom PET and SL lead to a change in treatment strategy. The accuracy of each modality will be analyzed separately. Secondary outcome parameters are diagnostic performance (sensitivity, specificity, positive and negative predictive value), morbidity and mortality, quality of life, cost reduction and cost-effectiveness. The hypothesis of this study is that adding PET and SL to additional staging in these patients will lead to a change of treatment strategy in 27% of patients, leading to an annual cost reduction in the Netherlands of €916.438 by reducing futile treatment.

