#### Investigated modalities

The modalities to be investigated in this study are both PET and SL in addition to the initial staging with gastroscopy and CT of patients with an advanced gastric cancer (cT3–4). Patients will undergo PET and SL according to the recently revised Dutch guidelines [15]. All patients will first undergo a PET, and if the PET does not show evidence of distant metastases a SL will be performed (Fig. 1). PET or SL may be omitted if it is deemed appropriate by the MDT or if it appears that a patient is not able to undergo one of both modalities.

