#### FDG-pet/CT

Preparation of patients for PET, and scanning and image reconstruction will be performed according to the institutional protocols of the participating centers, preferably incorporating guidelines of the European Association of Nuclear Medicine (EANM) / EANM Research Ltd. (EARL) and/or Netherlands Association of Nuclear Medicine (NVNG) [16]. In general, patients should refrain from strenuous exercise, and fast for at least 4 to 6 h before the injection of FDG. Patients should be pre-hydrated by drinking approximately 1 L of water in the 2 h before injection. Fasting blood glucose should preferably be below 11 mmol/L. After the injection of FDG, patients will remain seated or lying, and silent for 1 h in a warm room. A full body PET scan will be performed 60 min (range 55–75 min) after the injection of FDG, accompanied by a CT at the same scanning range. Scans are read, interpreted and reported by the nuclear medicine physicians of the respective participating centers. The report generally includes information regarding the FDG-avidity of the primary tumor and/or locoregional lymph nodes, and suspicion of distant metastases. For this study, the maximum standardized uptake values (SUVmax, corrected for body weight) of the primary tumor will also be registered. If the PET identifies new lesions that are possible metastases, a histological of cytological biopsy and/or additional imaging of a lesion is advised to confirm or exclude metastases.

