#### Staging laparoscopy

SL will be performed after the PET, prior to the initiation of treatment, and should be performed by or under supervision of a gastrointestinal or oncological surgeon. During staging laparoscopy, the goals are to evaluate the resectability of the primary tumor (T-stage) and to evaluate the presence or absence of peritoneal metastases. To evaluate the resectability of the tumor, a thorough inspection of the region of the stomach and tumor along with surrounding organs will be performed. In case of a tumor localized at the posterior wall of the stomach, it is advised to open the omental bursa and inspect it accordingly. To evaluate the presence or absence of peritoneal metastases, all quadrants of the peritoneal cavity and Douglas’ pouch will be inspected. In case of suspicious macroscopic lesions, biopsies will be taken and sent for histological review. When macroscopic lesions are present, all thirteen regions of the abdomen will be evaluated and the peritoneal cancer index (PCI) will be scored [17]. Cytology of the peritoneal cavity should be performed (500cm^3^ dispersed throughout all quadrants and Douglas’ pouch) as it is a promising prognostic factor with possible implications for treatment in the future [18, 19].

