### Statistical analysis

The primary outcome measures, change in treatment strategy of PET and SL, will be presented as a percentage. To evaluate the performance of PET and SL, sensitivity and specificity will be calculated. A separate analysis will be performed to assess whether both diagnostic modalities are accurate for various subgroups, for instance tumor types (Lauren classification: diffuse, intestinal and mixed). The quality of life of patients in this study will be compared to previous data from literature and to a retrospective cohort of patients who did not undergo PET and SL. Differences are tested using linear mixed-effects modeling, taking relevant patient characteristics into account. Missing values will be imputed using multiple imputation techniques. Statistical significance is defined as *p* < 0.05. Cost-effectiveness will be calculated, taking all relevant health-related costs into account, including costs arising from complications of medical treatment, and additional diagnostics arising from false-positive findings on PET. A model (Fig. 2) will be developed to compare health care costs with only CT. A budget impact analysis (BIA) will be performed, adhering to the newest guidelines and applying the societal, health insurance/third party payer and health care perspectives. Analyses will be performed for the combination of PET and SL and for both treatment modalities separately.

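### PET sensitivity for distant metastases may be overstated: about 19% of PET-negative patients are expected to be SL-positive, and many may lack an interpretable reference result for distant disease

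*Protocol article*

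**What the plan says.** All references are to the protocol article.

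- **Accuracy by modality.** Objectives states "The accuracy of each modality will be analyzed separately" and lists the measures: "Secondary outcome parameters are diagnostic performance (sensitivity, specificity, positive and negative predictive value". Statistical analysis repeats the intention: "To evaluate the performance of PET and SL, sensitivity and specificity will be calculated".
- **Order of tests.** Investigated modalities: "All patients will first undergo a PET, and if the PET does not show evidence of distant metastases a SL will be performed". The Discussion adds that SL is omitted once distant metastases on PET are confirmed by biopsy or further imaging.
- **Check on PET.** For new lesions that PET identifies, the FDG-PET/CT section says that "a histological of cytological biopsy and/or additional imaging of a lesion is advised to confirm or exclude metastases". The article describes no corresponding check for a negative PET.
- **What SL examines.** Staging laparoscopy: "the goals are to evaluate the resectability of the primary tumor (T-stage) and to evaluate the presence or absence of peritoneal metastases".
- **Expected yields.** In the cited US study the "combination of PET and SL identified additional metastases in 27% of patients", made up of "distant metastases by PET in 10% of patients, and peritoneal metastases by SL in 19% of patients (with an overlap of 2" percent. The Background thus assigns distant metastases to PET and peritoneal ones to SL.
- **Follow-up.** Time schedule plans follow-up of the patients, without restricting it by SL result and without giving its content.

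**The concern.** A false-negative PET can be counted only if the missed lesion comes to light some other way. The one route the Background describes is distant disease that appears soon after curative-intent treatment. PET-negative, SL-positive patients are the group most likely to leave that route, because a positive SL can lead to curative surgery being withheld. SL does not fill the gap, since its stated goals are resectability and the peritoneum. If a distant lesion is seen later in a patient with known peritoneal metastases, it is hard to say whether PET missed it at baseline or whether the disease has progressed.

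PET-negative patients are therefore verified differently according to their SL result, and this follows from the test sequence. Two simple ways of handling the unverified group both favour PET:

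- Counting them as true negatives hides any misses among them.
- Excluding them removes those misses from the denominator of sensitivity, while PET-positive patients who also have peritoneal disease stay in the numerator because they do not go on to SL.

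At stake is the separate statement on PET accuracy, in a study whose results are meant to feed an updated guideline.

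**Working it through.** **Inputs from the Background (cited US study).** PET yield 10%, SL yield 19%, both 2%.

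**Reproducing the article's figure.** 10 + 19 − 2 = 27%, which matches the stated combined yield.

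**Size of the group, per 100 patients.**
- PET-positive: 10. PET-negative: 90.
- PET-negative and SL-positive: 19 − 2 = 17.
- PET-negative and SL-negative: 90 − 17 = 73.
- Share of PET-negatives who are SL-positive: 17/90 = 18.9%.
- At the minimum of 239 patients: 0.17 × 239 ≈ 41 of 0.90 × 239 ≈ 215. At the expected 543: about 92 of 489.

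**Assumptions not in the documents.** All 10 PET-positives are true positives. Every SL-negative patient is verified and no SL-positive patient is. The rate of missed distant metastases is q0 in the 73 and q1 in the 17.

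**Formulas.**
- Missed cases = 73·q0 + 17·q1.
- Sensitivity = 10 / (10 + missed cases).
- NPV = 1 − missed cases / 90.
- Apparent sensitivity, under either handling = 10 / (10 + 73·q0).
- Apparent NPV, group counted as true negatives = 1 − 73·q0 / 90.
- Apparent NPV, group excluded = 1 − q0.

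**Apparent values at q0 = 3%** (73 × 0.03 = 2.19 observed misses).
- Sensitivity: 10/12.19 = 82.0%.
- NPV, counted as true negatives: 1 − 2.19/90 = 97.6%.
- NPV, excluded: 1 − 2.19/73 = 97.0%.

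**Values with the hidden misses included, q0 = 3%.**

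| q1 in the 17 | Missed cases | Sensitivity | NPV |
|---|---|---|---|
| 0% | 2.19 | 82.0% | 97.6% |
| 3% (equal) | 2.19 + 0.51 = 2.70 | 10/12.70 = 78.7% | 97.0% |
| 6% (double) | 2.19 + 1.02 = 3.21 | 10/13.21 = 75.7% | 96.4% |
| 100% (bound) | 2.19 + 17 = 19.19 | 10/29.19 = 34.3% | 78.7% |

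With equal rates the hidden share of all misses is 0.51/2.70 = 19%. With the rate doubled it is 1.02/3.21 = 32%.

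**A higher miss rate, q0 = q1 = 5%.** Apparent sensitivity is 10/13.65 = 73.3%, against 10/14.50 = 69.0%. NPV counted as true negatives is 95.9%, against 95.0%.

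**Which q1 is plausible.** In the cited study PET was positive in 2/19 = 10.5% of SL-positive patients and 8/81 = 9.9% of the rest. That is compatible with similar rates of distant disease in both groups, and so with the equal-rate row, although the numbers are small.

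**Any metastasis as target.** A positive SL then counts as a PET miss, so sensitivity is at most 10/27 = 37.0%. Misses found at surgery or in follow-up would lower it further.

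**The case against.** The strongest reply is that the article fixes no faulty handling. It says only that accuracy will be analysed for each modality. The reference standard, the target condition and the treatment of unverified patients may all stand in a full protocol or analysis plan that is not shown, and their absence from an article is no fault. That is right, and the point does not rest on it. It rests on a stated objective and a stated sequence which together cannot give an unbiased PET sensitivity for distant disease unless this group is handled explicitly.

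Second, PET's target may be any metastasis. The Discussion does mention PET's performance for nodal, liver and peritoneal disease. Under that reading a positive SL is itself a reference result and the under-count largely disappears. This stands, but sensitivity is then capped at about 37% on the cited figures, so the choice of target matters far more than the bias.

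Third, a reader might infer more than the documents support:

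- *That these patients never get a reference result.* Follow-up is planned without restriction by SL result, and later imaging may settle some of them.
- *That every positive SL ends curative treatment.* The primary outcome also includes a changed chemotherapy regimen, and the Discussion mentions possible entry into HIPEC trials.
- *That NPV is biased under either handling.* With exclusion and equal miss rates, both figures are 97.0%.
- *That biased PET accuracy drives the cost model.* The decision tree is not shown, so its inputs cannot be checked.

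**Conclusion.** The point holds as a possible overstatement of PET sensitivity for distant metastases. The group concerned is 18.9% of PET-negatives, if the cited US yields carry over to this cohort. The direction for sensitivity is the same under both simple handlings, provided at least one unverified patient has a missed lesion. If none has, there is no bias in sensitivity. For NPV the direction depends on the handling: counting the group as true negatives overstates it, while exclusion overstates it only if the miss rate is higher in SL-positive than in SL-negative patients.

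The size rests on miss rates that the documents do not give. At equal rates of 3% the shift is about 3 points in sensitivity and 0.6 points in NPV. A sensitivity of 34% would require all 17 SL-positive patients per 100 to have distant metastases missed by PET. It marks the edge of what unverified data allow and should not be read as an expectation.

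Severity is minor. A secondary outcome is affected, and the primary outcome, the proportion with a change in treatment strategy, is untouched.

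**What to change.** In the analysis plan:

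1. Name PET's target condition. For distant (non-peritoneal) metastases, classify PET-negative, SL-positive patients as unverified unless a follow-up or imaging result settles their status.
2. Report PET sensitivity and NPV with an equal-miss-rate estimate, applying the miss rate in verified PET-negatives to the unverified (the Begg–Greenes approach). Add an upper bound with none of the unverified missed and a lower bound with all missed.
3. Beside these, report PET sensitivity for any metastasis found by PET, SL, surgery or follow-up.
4. If PET accuracy is an input to the PET-only cost model, vary it over the same range.

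This takes a few sentences of analysis wording and extra table rows. It needs no new data and changes no patient's care. The drawback is that PET accuracy will be reported less favourably and as a range.

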### Study design

The study design is a prospective observational cohort study. All patients with a locally advanced tumor who are candidates for gastrectomy with curative intent will be invited to participate in this study. A locally advanced tumor is defined as a transmural tumor invading the outer layer of the stomach (cT3–4 according to the 7th edition of the American Joint Committee on Cancer TNM staging system [12]), objectified on CT [13].

### Study population

The study population consists of patients with a surgically resectable, advanced gastric adenocarcinoma (cT3–4b, N0–3, M0), who are scheduled for treatment with curative intent after initial staging with gastroscopy and CT. Patients’ inclusion and exclusion criteria are defined as follows:

Inclusion criteria:

• Histologically proven adenocarcinoma of the stomach or esophagogastric junction (Siewert type III) as observed by gastroscopy.

• Underwent evaluation with CT of the abdomen and chest.

• Surgically resectable, advanced gastric cancer (cT3–4b, N0–3, M0), as determined by the multidisciplinary team (MDT).

• Intention to perform a potentially curative gastrectomy with or without perioperative treatment.

Exclusion criteria.

• Siewert type I-II esophagogastric junction tumor.

• Unfit or unwilling to undergo surgery.

### Study protocol

#### Initial staging

Initial staging should be performed according to national guidelines, including at least gastroscopy with tumor biopsies and a CT of the thorax and abdomen. Endoscopic Ultrasonography (EUS) may be performed optionally. In case of a cT3–4 tumor (defined as a transmural tumor invading the outer layer of the stomach) [13], patients will be invited to participate in this study and thereby give permission to collect and analyze their data. Differentiation between cT2 and cT3 tumors is not always possible with initial staging. In case of considerable doubt whether a tumor is cT2 or cT3, patients will be included if deemed appropriate by the MDT. As part of a side study, an expert panel will review all CT-scans to reach consensus on the clinical T-stage.

#### Patient inclusion

If eligible for treatment with curative intent by the MDT, patients will be invited to participate in this study. Patients will be informed and included at the outpatient department of one of the Dutch investigational centers or its associated hospitals. As this study does not allocate patients to study interventions other than usual care, as recommended by the new Dutch guidelines, this study does not fall within the Medical Research Involving Human Subjects Act (WMO). Patients will be asked to sign informed consent form to confirm that they know that their data will be anonymously used for research purposes, and approve to fill out quality of life questionnaires, making use of the previously reported infrastructure of POCOP [14].

#### Investigated modalities

The modalities to be investigated in this study are both PET and SL in addition to the initial staging with gastroscopy and CT of patients with an advanced gastric cancer (cT3–4). Patients will undergo PET and SL according to the recently revised Dutch guidelines [15]. All patients will first undergo a PET, and if the PET does not show evidence of distant metastases a SL will be performed (Fig. 1). PET or SL may be omitted if it is deemed appropriate by the MDT or if it appears that a patient is not able to undergo one of both modalities.

**Fig. 1 Fig1:**

Study Flowchart. CT: computed tomography; cT3–4: advanced tumor with clinical T-stage 3 or 4.; MDT: Multidisciplinary Team; PET: fluorodeoxyglucose positron emission tomography with CT; SL: Staging Laparoscopy

#### FDG-pet/CT

Preparation of patients for PET, and scanning and image reconstruction will be performed according to the institutional protocols of the participating centers, preferably incorporating guidelines of the European Association of Nuclear Medicine (EANM) / EANM Research Ltd. (EARL) and/or Netherlands Association of Nuclear Medicine (NVNG) [16]. In general, patients should refrain from strenuous exercise, and fast for at least 4 to 6 h before the injection of FDG. Patients should be pre-hydrated by drinking approximately 1 L of water in the 2 h before injection. Fasting blood glucose should preferably be below 11 mmol/L. After the injection of FDG, patients will remain seated or lying, and silent for 1 h in a warm room. A full body PET scan will be performed 60 min (range 55–75 min) after the injection of FDG, accompanied by a CT at the same scanning range. Scans are read, interpreted and reported by the nuclear medicine physicians of the respective participating centers. The report generally includes information regarding the FDG-avidity of the primary tumor and/or locoregional lymph nodes, and suspicion of distant metastases. For this study, the maximum standardized uptake values (SUVmax, corrected for body weight) of the primary tumor will also be registered. If the PET identifies new lesions that are possible metastases, a histological of cytological biopsy and/or additional imaging of a lesion is advised to confirm or exclude metastases.

